### Interventions

Bradycardia is defined as a HR of <60 beats per minute. If HR is below 50 beats per minute with hypotension, atropine or ephedrine will be administered. Tachycardia is defined as a HR > 100 beats per minute. If the depth of anesthesia and the degree of analgesia are sufficient and a HR > 90 beats per minute is observed, esmolol will be administered. Hypotension is defined as systolic pressure <90 mmHg or diastolic pressure <50 mmHg. Hypertension is defined as over 20% of the baseline blood pressure. If hypotension or hypertension occurs, metaraminol, urapidil hydrochloride or nicardipine hydrochloride will be administered.

### Objectives

The present study aims are:1) To screen differential sensitivity to sevoflurane in patients;2) To find differential metabolites in group H compared with group L using plasma metabolomics;3) To find differential SNPs and genes in group H compared with group L using WES, GWAS and bioinformatics.

### Outcomes

The primary outcome is the incidence of high sensitivity to sevoflurane in patients. Secondary outcomes include the following:1) The average ETsevo at stable state;2) Tracheal extubation time;3) Incidence of intraoperative awareness;4) The use of vasoactive drugs;5) Incidence of postoperative nausea and vomiting.

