## Abstract

**Introduction:** Different sensitivity to volatile anesthetics in *Drosophila*, nematodes and mice is related to mutation of energy metabolism genes. In clinical practice, we find that the end-tidal sevoflurane concentration (ET_sevo_) differs among patients at the same depth of anesthesia, indicating that the sensitivity to sevoflurane varies among patients. However, the underlying mechanism remains unclear. The sensitivity of an anesthetic is associated with the postoperative outcomes of patients and the mechanism of action of volatile anesthetics. We therefore propose this protocol to determine whether differences in metabolite profile and genetic variations contribute to patients’ sensitivity to volatile anesthetics.

**Methods and Analysis:** This is a single-centre, prospective observational study. 720 patients undergoing abdominal surgery were included. General anesthesia was induced with inhaled sevoflurane, a bolus of sufentanil (0.2–0.4 μg/kg) and *cis*-atracurium (0.2–0.3 mg/kg). The end-tidal sevoflurane concentration (ET_sevo_) was adjusted to maintain a BIS (bispectral index) value between 40–60. The mean ET_sevo_ from 20 min after endotracheal intubation to 2 h after the beginning of surgery (steady state) was calculated for each patient. Patients were further divided into a high-sensitivity group (mean ET_sevo_ – SD) and a low-sensitivity group (mean ET_sevo_ + SD) to investigate the sensitivity to sevoflurane. Cases were paired from the high-sensitivity group (group H) and low-sensitivity group (group L) according to age, sex, body mass index (BMI), *ASA* physical status classification, vital signs, BIS, ephedrine use, sufentanildose, and *cis*-atracurium dose at anesthesia induction and steady state. Differences in metabolite levels, single nucleotide polymorphisms (SNPs) and protein-coding gene sequence variations between group H and group L will be determined through plasma metabolomics, whole-exome sequencing (WES), genome-wide association study (GWAS), and bioinformatics analyses. These results will be analysed to determine the reasons for the differential sensitivity to sevoflurane in humans.

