**FIGURE 1 F1:**
[figure not shown]
Flow diagram of the study.

The mean ETsevo from 20 min after endotracheal intubation to 2 h after starting surgery (steady state) was calculated in all patients. The data with normal distribution was present with mean ± standard deviation (SD). High-sensitivity was defined by an ET_sevo_ at least 1 standard deviation lower than the mean. Low-sensitivity was defined by an ET_sevo_at least 1 standard deviation higher than the mean. We have paired patients from the high-sensitivity group (group H) and low-sensitivity group (group L) according to age, sex, operation method (laparotomy/laparoscopic surgery), body mass index (BMI), *ASA* physical status classification, vital signs, end-tidal partial pressure of carbon dioxide (P_ET_CO_2_), BIS values, ephedrine use, and the sufentanil and *cis*-atracurium doses at anesthesia induction and steady state. We performed follow up to determine the occurrence of intraoperative awareness, postoperative nausea and vomiting in patients at the post-anesthesia care unit, and at postoperative day 1 and 3.

The plasma collected before anesthesia induction and at 2 h after starting surgery in group H and group L was labelled with group H-before, H-after, L-before and L-after, respectively. Quality control of all plasma samples were implemented. The stability of the instrument and the acquired signal were monitored in real-time to ensure the quality of process (process quality control). The chromatography mass spectrometry may be affected by the aging circuit board, humidity, temperature, vibration and other factors, which will cause the fluctuation of acquired signal. Therefore, data processing is required to obtain high quality data (data quality control).

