### Sample Size

In this study, the sample size was calculated based on our preliminary experimental results. We estimate the incidence of high-sensitivity patients as 12%, with a power of 80% and *α* = 0.05 (two sided); thus, we need 329 patients in each group. Assuming a drop-out rate of 4% during the study, 342 patients per group are required. Therefore, a total of 700 patients are required in our study.

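### The primary outcome, incidence of high sensitivity, is cut at the cohort's own mean minus 1 SD, so it reflects only the shape of the ETsevo distribution and cannot show how common high sensitivity is

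*Protocol article*

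**What the plan says.** - **Outcomes:** "The primary outcome is the incidence of high sensitivity to sevoflurane in patients". The average ETsevo at stable state is the first secondary outcome.
- **Study Design (text after Figure 1):** each patient's mean ETsevo "from 20 min after endotracheal intubation to 2 h after starting surgery (steady state) was calculated in all patients". The next sentence reads "The data with normal distribution was present with mean ± standard deviation (SD"). Then come the two cut-offs: "High-sensitivity was defined by an ET_sevo_ at least 1 standard deviation lower than the mean", and low sensitivity as a value "at least 1 standard deviation higher than the mean".
- **Abstract:** the same rule, "Patients were further divided into a high-sensitivity group (mean ET_sevo_ – SD) and a low-sensitivity group (mean ET_sevo_ + SD").
- **Sample Size:** "We estimate the incidence of high-sensitivity patients as 12%, with a power of 80% and" a two-sided alpha of 0.05. This leads to 329 per group, 342 per group after 4% drop-out, and 700 in total. The 12% is attributed to preliminary results, whose size and cut-off are not stated.
- **Objectives:** the first aim is to screen for differential sensitivity. The second and third compare groups H and L on metabolites, SNPs and genes.

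No absolute, clinical or externally derived ETsevo threshold appears anywhere in the article.

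**The concern.** An incidence is informative when the condition is defined independently of the sample in which it is counted. Here the threshold is recalculated from the patients being counted. If every patient needed half as much sevoflurane, the mean and the SD would both halve, the cut-off would move with them, and the same patients would be labelled highly sensitive. Two hospitals with very different sevoflurane requirements would report the same incidence if their distributions had the same shape.

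This is the outcome named as primary and the one on which the sample size is based. A reader of the eventual report would take a figure near 16% as the frequency of a clinical trait, when most of it follows from the definition.

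**Working it through.** **Inputs.** Rule: ETsevo ≤ mean − 1 SD of the cohort (Study Design, Abstract). Recruited N = 720 (Study Design). Planning incidence 12% (Sample Size). The distributions below are assumptions, because the article gives no ETsevo data.

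**1. The plan's own figure.** The 12% cannot be reproduced, because its source data are not described. Nor do the 329 per group follow from the printed inputs: no comparator rate, difference or precision is given. At N = 720, 12% is 0.12 × 720 = 86 patients.

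**2. Invariance.** Replace each value x by a + bx with b > 0. The mean becomes a + b·mean, the SD becomes b·SD, and the cut-off becomes a + b(mean − SD). The same patients fall below it, so level and spread drop out.

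**3. Value under normality.** Φ(−1) = 0.1587, and 0.1587 × 720 = 114 patients.

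**4. Sampling range under normality.** The cut-off is estimated from the same sample, so the large-sample variance of the proportion is [p(1 − p) − 1.5φ(1)²]/n, where φ(1) = 0.2420:
- p(1 − p) = 0.1587 × 0.8413 = 0.1335
- 1.5 × 0.2420² = 0.0878
- SD = √[(0.1335 − 0.0878)/720] = 0.0080
- 95% range = 15.87% ± 1.96 × 0.80 = 14.3% to 17.4%

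Simulated cohorts of 720 with mean/SD of 1.8/0.3, 1.2/0.1 and 2.5/0.8, each classified by its own mean and SD, all gave 15.8% to 15.9% with the same range of 14.3% to 17.4%.

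**5. Dependence on shape.**

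| Shape | Share at or below mean − 1 SD |
|---|---|
| Normal | 15.9% |
| Gamma, skewness 0.5 | 15.6% |
| Lognormal, CV 0.3 | 14.3% |
| Lognormal, CV 0.5 | 10.9% |
| t, 5 df | 12.7% |
| Uniform | 21.1% |

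Two of these by hand. Uniform on (0, 1): 0.5 − 1/√12 = 0.211. Lognormal with CV 0.5: σ = √ln(1.25) = 0.472, and Φ[(ln 0.5 + σ²/2)/σ] = Φ(−1.23) = 0.109.

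**6. Does it follow a real sensitive subgroup?** Take a normal population in which a share π of patients is shifted down, and classify by the mixture's own mean and SD.

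| True share π | Measured, 1.5 SD shift | Measured, 3 SD shift |
|---|---|---|
| 0% | 15.9% | 15.9% |
| 5% | 15.6% | 13.3% |
| 12% | 15.6% | 14.2% |
| 20% | 16.0% | 17.2% |
| 30% | 16.4% | 20.0% |
| 50% | 16.6% | 19.0% |

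With the smaller shift the figure barely moves. With the larger one it falls, rises and falls again. In both cases, adding a 5% sensitive subgroup lowers the measured incidence.

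**7. Is 12% compatible with normality?** For normal samples classified by their own mean − SD, the simulated 95% range is 10.0% to 22.0% at n = 50, 11.3% to 20.0% at n = 80 and 12.0% to 20.0% at n = 100. At 720 it is 14.3% to 17.4%. A preliminary sample of up to about 100 could therefore have given 12% from normal data.

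**The case against.** **The rule is a sensible way to choose extremes.** This stands. Taking patients beyond ±1 SD for the metabolomic and genetic comparisons is a workable selection rule, and those comparisons do not use the incidence figure. A reader might infer that the second and third aims fail as well; nothing on this point supports that.

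**The result is not a constant.** This also stands. Calling it fully predetermined would go too far, since skew, heavy tails or a bimodal distribution change it. But information about shape is not information about how common sensitivity is, as step 6 shows.

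**The level of ETsevo is reported anyway.** True: the average at stable state is a secondary outcome. The fault lies in which quantity is called primary and what it is said to measure.

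**Details may sit in the full protocol or analysis plan.** This does not help, because the article itself states both the outcome and its definition.

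Two stronger readings are tempting and should not be drawn:
- *That 12% shows ETsevo is not normal, or contradicts the definition.* It lies outside the range for 720 patients, but it came from preliminary data of unstated size and threshold. Step 7 shows that it can arise from a normal sample of up to about 100.
- *That the planned confidence interval is wrong.* A binomial SD at N = 720 would be √(0.1335/720) = 1.36 points against 0.80 in step 4. However, the article plans no binomial interval for the incidence, so there is no such analysis to fault.

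**Conclusion.** The point holds. As defined, the primary outcome is unaffected by the level and spread of ETsevo. It is about 15.9% (14.3% to 17.4% at N = 720) in a near-normal cohort and departs from that only with shape, to about 11% or 21% in the examples. It does not answer the first aim and cannot be compared across cohorts.

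This rests on two things. First, the mean and SD in the definition are those of the study cohort; that is the natural reading of Study Design and the Abstract, and no other source is offered. Second, the 15.9% needs approximate normality; the invariance to level and spread does not. The gap between 12% and 15.9% needs explaining but proves nothing by itself.

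The damage is confined to the primary outcome and to the sample-size statement built on it.

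**What to change.** 1. **Primary outcome:** replace it with the distribution of steady-state ETsevo in the full cohort: mean, SD, and 5th to 95th percentiles, each with a confidence interval. The mean, now secondary, moves into the primary outcome.
2. **±1 SD rule:** keep it only to select groups H and L for the metabolomic and genetic comparisons, and drop the incidence claim.
3. **Sample Size:** restate it as the precision obtained at the recruited N. Under normality with 720 evaluable patients, the 95% half-widths are:
   - mean: 1.96/√720 = 0.073 SD
   - SD: 1.96/√(2 × 719) = 5.2% of its value
   - 5th or 95th percentile: 1.96 × √(0.05 × 0.95/720)/0.103 = 0.15 SD, where 0.103 is the normal density at that percentile

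   Also state the size and threshold of the preliminary data behind the 12%, or remove that figure.

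Do not substitute the preliminary data's mean − SD as a fixed cut-off. If those patients come from the same population, the expected incidence is again about 16% (simulated 16.3% for a preliminary sample of 50 and 16.1% for 100). Noise in the cut-off would widen the range to roughly 9% to 26% and 10% to 23%, and an interval computed from the 720 alone would ignore that noise. It also comes late, because Study Design reports recruitment and pairing as done, and a new cut-off could change who belongs to H and L.

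**Cost:** edits to the outcome, sample-size and analysis text, and loss of the headline incidence figure. No new data, no change in group membership and no re-pairing are needed.

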### Inclusion Criteria

Consenting patients will be eligible if.1) Aged 18–65 years;2) Undergoing radical gastrectomy or colorectal surgery;3) In American Society of Anesthesiologists (ASA) category 1–2;4) Operation time duration exceeding 2 h;5) Written informed consent provided.

### Exclusion Criteria

Patients will be excluded if any of the following exists:1) Allergy to volatile anesthetics;2) Cerebrovascular diseases, including cerebral infarction, transient cerebral ischemia, intracranial hematoma, cerebrovascular malformation, and cerebral hemorrhage;3) Cardiovascular diseases, including coronary heart disease, arrhythmia, heart failure, valvular disease, and congenital heart disease;4) Alcohol addiction;5) Malignant hyperthermia;6) Abnormal liver or renal function.

### Sample Size

In this study, the sample size was calculated based on our preliminary experimental results. We estimate the incidence of high-sensitivity patients as 12%, with a power of 80% and *α* = 0.05 (two sided); thus, we need 329 patients in each group. Assuming a drop-out rate of 4% during the study, 342 patients per group are required. Therefore, a total of 700 patients are required in our study.

### Statistical Methods

Statistical analyses will be performed using SPSS (Version 22.0, IBM Corp., Armonk, NY, United States). Normally distributed data will be presented as the mean ± SD, whereas non-normally distributed data will be presented as the median and interquartile range. Analysis of variance will be used for continuous variables. Categorical data will be presented as numbers and compared using the chi-squared test. Groups will be compared using Student’s *t*-test (normally distributed data) or the Mann-Whitney *U* test (nonnormally distributed data). After identification of differential metabolites and multivariate statistical analysis, metabolites with significant differences between groups will be screened by variable importance in projection (VIP) of model variables with orthogonal partial least squares discriminant analysis (OPLS-DA) and the *p* value of the *t* test for univariate statistical analysis. Metabolites with *p* < 0.05 and VIP ≥1 were considered differential metabolites between comparisons. To identify correlations between metabolite levels and the amount of sevoflurane exposure, multivariate linear regression or Pearson’s correlation analysis will be performed using MetaboAnalyst 4.0 software.

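### For the clinical secondary outcomes the article states only group tests, and its only sensitivity groups are the ±1 SD tails of ETsevo; regression on continuous ETsevo in the whole cohort would use data already collected and lose less power

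*Protocol article*

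**What the plan says.** **Exposure.** Study Design (text below Figure 1) says that the mean ETsevo from 20 min after intubation to "2 h after starting surgery (steady state) was calculated in all patients". The same section recruits 720 patients.

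**Groups.** "High-sensitivity was defined by an ET_sevo_ at least 1 standard deviation lower than the mean"; low sensitivity is the mirror image above the mean. H and L patients are then paired on a long list of variables that includes ephedrine use. The number of pairs is not given.

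**Outcomes.** After average ETsevo, Outcomes lists these secondary outcomes: "Tracheal extubation time;3) Incidence of intraoperative awareness;4) The use of vasoactive drugs;5) Incidence of postoperative nausea and vomiting". No contrast is attached to any of them.

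**Tests.** Statistical Methods offers analysis of variance, Student's t-test and Mann-Whitney U, and adds: "Categorical data will be presented as numbers and compared using the chi-squared test". It does not say which groups or outcomes these tests serve. Regression or correlation with sevoflurane exposure is planned there and in Study Design, but only for metabolite levels.

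**Aims.** Objectives names H versus L explicitly for metabolites and for SNPs and genes, and for nothing else.

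**The concern.** The Abstract and the Discussion motivate the study partly by a possible link between anesthetic sensitivity and postoperative outcomes. Sensitivity is measured on a continuous scale in everyone, and extubation time, vasoactive drug use and PONV are routine or follow-up data. Selecting the extremes makes sense for metabolomics and exome sequencing, where each sample costs money. That reason does not apply to outcomes that can be analysed in the whole cohort at no extra cost.

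If the stated tests are applied to the stated groups, the middle of the cohort does not contribute, nor does any tail patient without a pair, and variation of ETsevo within each tail is ignored. A real association is then more likely to be missed. A contrast of extremes also cannot show the shape of the relation over the usual ETsevo range.

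**Working it through.** **Inputs.** From the article: 720 patients recruited; cuts at mean ± 1 SD; two-sided 5%; an expected 12% with high sensitivity. Assumed: normal ETsevo, a linear relation with the outcome, and a full-cohort power used as the benchmark, because the article states no effect or SD for any clinical outcome.

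**1. The plan's own figure.** Sample Size states "0.05 (two sided); thus, we need 329 patients in each group", for 80% power and 12% incidence. The comparison rate is missing, so 329 cannot be derived from the stated inputs. Back-solving, 12% versus 20% gives 329 (pooled, no continuity correction). The article inflates this to 342 per group for 4% drop-out; 2 × 342 = 684, stated as 700. Nothing here concerns a clinical outcome. Nor can 342 be the size of H or L, as step 2 shows.

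**2. Group sizes.** Under normality each tail beyond 1 SD holds t = 0.1587, so 720 × 0.1587 ≈ 114 patients. The middle is 1 − 2 × 0.1587 = 68.3%, about 492 patients. With 12% in each tail, there are about 86 per tail and 76% (547) in the middle. The 68% depends on shape: the share within 1 SD is 58% for a uniform distribution, 71% for mild right skew and 75% for a t distribution with 5 df.

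**3. Relative information.** Let the slope be β per SD of ETsevo and the residual SD σ.
- Full cohort: noncentrality = β√N/σ.
- H versus L with all tail patients: the groups lie d = 2φ(c)/t SDs apart, where c is the cut. Noncentrality = dβ√(Nt/2)/σ.
- Ratio: r = d√(t/2). If a share m of tail patients is retained after pairing, the ratio becomes r√m.

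For ±1 SD: d = 2 × 0.2420/0.1587 = 3.050; r = 3.050 × √0.0793 = 0.859; information r² = 0.738.

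For 12% tails: d = 3.334; r = 3.334 × √0.06 = 0.817; r² = 0.667.

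**4. Power.** At 80% in the full cohort, power = Φ(2.802 × r√m − 1.960), where 2.802 = 1.960 + 0.842.
- ±1 SD, all paired: Φ(2.407 − 1.960) = 67.3%.
- 12% tails, all paired: Φ(2.288 − 1.960) = 62.9%.
- ±1 SD, 75% paired: Φ(2.802 × 0.859 × √0.75 − 1.960) = 55.0%.

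Other benchmarks:

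| Full-cohort power | ±1 SD, all paired | ±1 SD, 75% paired | 12% tails, all paired |
|---|---|---|---|
| 70% | 56.9% | 45.6% | 52.7% |
| 80% | 67.3% | 55.0% | 62.9% |
| 90% | 79.5% | 67.4% | 75.4% |
| 99% | 95.8% | 89.0% | 93.8% |

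**5. Simulation check** (N = 720, 4000 runs, ±1 SD cuts in the simulated sample). Pairing was represented only by retaining 75% of the smaller tail in each group.
- Continuous outcome: full cohort 79.3%, H versus L 65.5%, with 75% retained 52.9%.
- Binary outcome, 30% base rate: 80.9%, 67.0% and 55.1%.
- Binary outcome, 15% base rate: 80.7%, 66.7% and 52.9%.
- Three-group chi-squared test (low, middle, high) in all patients: 58% and 56% for the two binary cases. Keeping the middle as a third category does not recover the loss.

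**6. Ephedrine.** It is a pairing variable in Study Design, and vasoactive drug use is an outcome. Pairs made alike on ephedrine are made alike on part of that outcome, so a paired comparison would be drawn towards no difference.

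**The case against.** The strongest reply is that H versus L for these outcomes is not in the text. Objectives ties that contrast to metabolites, SNPs and genes only. The secondary outcomes include average ETsevo, which cannot sensibly be tested between groups defined by ETsevo, and two others are incidences, so the list may be meant as whole-cohort description. Follow-up is described for patients in general, and it starts in the recovery unit, before a cohort mean and SD could be known. No paired test is named. The article also refers to a full protocol, and detailed models may sit there.

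Much of this stands. A reader might infer that paired H versus L is the plan's only comparison for the clinical outcomes; the article does not say so. A reader might also take 68% as a minimum loss of patients and 13 points as a minimum loss of power. Neither is a bound: the first needs normality, and the second depends on a benchmark power that the article does not supply. Nor does the 12% figure by itself give 55% power. That result comes from combining 86 patients per tail with the mean distance of a 15.9% tail; a true 12% tail lies further out and gives 62.9%. Finally, the primary outcome and average ETsevo still use the whole cohort, so no data are discarded from the study.

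What the reply does not remove is that the methods actually stated are group tests. Reading analysis of variance as low, middle and high groups still categorises ETsevo. If the outcomes are only to be described, the link that motivates the study goes untested. The point therefore concerns the stated method and is not a complaint about missing detail.

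**Conclusion.** The point holds in a limited form. Under the tests and groups the article states, any comparison of extubation time, vasoactive drug use or PONV by sensitivity would categorise a continuous variable already calculated in all patients. With normal ETsevo, a linear relation and 80% full-cohort power, H versus L costs about 13 points of power without pairing loss, about 17 with 12% tails, and about 25 if three quarters of tail patients are paired. Without pairing loss the cost falls to 10.5 points at 90% full-cohort power and 3.2 at 99%. The real number of pairs and the real effects are unknown.

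This is a worthwhile, inexpensive improvement for secondary outcomes. It does not touch the primary outcome or the case for sampling extremes in the laboratory work.

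**What to change.** In Statistical Methods, add wording to this effect:

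> Tracheal extubation time, PONV and use of vasoactive drugs will be related to sensitivity in all patients with a steady-state mean ETsevo, by regression on ETsevo as a continuous variable (linear regression on log extubation time; logistic regression for binary outcomes). Models will be adjusted for age, sex, BMI, ASA class, operation method, mean BIS and the induction doses of sufentanil and cis-atracurium, with a spline or quadratic term to check linearity. Ephedrine will not be a covariate for the vasoactive-drug outcome. Comparisons of these outcomes between groups H and L are descriptive.

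Keep the paired groups for metabolomics and sequencing. Report awareness as a count over the whole cohort, since events are likely to be too few to model.

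The cost is a few sentences and standard models in SPSS, which the article already names; no further patients, samples or assays are needed. The downside is that an effect per unit of ETsevo is less simple to present than two groups and relies on a functional form that has to be checked.
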